#### Post-kind challenge overall impact

The measure includes 10 items pertaining to the effects of the Nextdoor KIND Challenge. Six items (looking forward to being with neighbours; more connected to neighbours; more socially confident; form new friendships; more connected to community; more positive feelings will be assessed using a Likert scale ranging from 1 (extremely disagree) to 5 (extremely agree) with higher responses reflecting greater success of the KIND Challenge. The remaining 4 items were recorded in an open-ended format allowing participants to explain what can help them feel more connected, what being connected means to them, what prevented participants from connecting and to provide feedback about how the KIND Challenge was ran. These questions were specifically developed for the study (see Supplementary Table 1 – section e).

#### Follow up KIND challenge activity

At 1 month follow-up**,** participants will be asked if they have been in contact with their neighbours in the past month (Yes/No). Participants are asked if they have *continued* with the Kindness activity, if so, which activity or activities they chose to continue. Participants will be asked how frequently they completed the activity (1 = once to 4 = more than 5 times), the duration (1 = less than 10 min to 5 = more than 2 h), and how connected they felt to others after completing the activity (1 = not at all to 10 = very). If they had not continued a Challenge activity, participants will be asked to report the main reasons for not continuing with the KIND Challenge activity in a textbox provided. These questions were specifically developed for the study (see Supplementary Table 1 – section f).

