Hypothesis 1 (H1): There will be a reduction in loneliness in participants assigned to the Nextdoor KIND Challenge groups compared to the waitlist control group post the 4-week intervention.Hypothesis 2 (H2): There will be a reduction in social isolation in participants assigned to the Nextdoor KIND Challenge groups compared to the waitlist control group post the 4-week intervention.Hypothesis 3 (H3): There will be an improvement in neighbourhood relationship quality and contact outcomes (a) social cohesion and trust, (b) perception that their neighbourhood is improving, (c) higher importance around getting to know their neighbours, (d) more likely to be classed as having a supportive neighbour network than not, (e) have lower neighbourhood conflict, and (f) increased number of neighbourhood contacts, in participants assigned to the Nextdoor KIND Challenge groups compared to the waitlist control group post the 4-week intervention.Hypothesis 4 (H4): There will be an improvement in mental health secondary outcomes, lower (a) depression and (b) social anxiety, (c) stress, and greater (d) quality of life, and (e) positive affect, in participants assigned to the Nextdoor KIND Challenge groups compared to the waitlist control group post the 4-week intervention.

While it is vital to investigate the impact of KIND Challenge post intervention, it is possible for impact on outcomes to be distal; that is indirect effects caused by changes in proximal outcomes. The KIND Challenge aims to reduce loneliness and social isolation, which may lead to later distal impact on other outcomes. Capturing impact at one-month follow-up after the completion of the KIND Challenge enables modelling the maintenance of intervention effects, i.e., are effects sustained at one-month or are sleeper effects present? In addition to understanding whether effects of the intervention are sustained, it is also important to know whether the intervention itself is sustainable. The KIND Challenge acts are positive, engaging, and feasible to the average individuals, and thus designed to be sustainable.
Hypothesis 5 (H5): The Nextdoor KIND Challenge effects noted in H1–4 above will be maintained at one-month follow-up for the participants randomly allocated to KIND Challenge group.Hypothesis 6 (H6): The KIND Challenge is sustainable, participants assigned to the KIND Challenge will continue engaging in acts of kindness at one-month follow-up.

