#### Post-KIND challenge activity

*Post intervention,* participants will be asked if they completed either their nominated KIND Challenge activity or any KIND Challenge activity over the past month. Type of support can be categorized based on participant selection. Participants can also select “other” activities that were not listed. If the “other” box activity is selected, participants are asked to describe the activity in detail via a free text entry box. Responses in the free text box entry will be coded independently by two research assistants not related to this trial. Inter-rater reliability between coders will be calculated to ensure adequate reliability of categorization. For each activity, participants will be asked how frequently they completed the activity (1 = once to 4 = more than 5 times), the duration of the activity (1 = less than 10 min to 5 = more than 2 h), how connected to others they felt after completing the selected activity (1 = not at all connected to 10 = very connected). They can select more than one activity and will rate each activity according to those scales. If participants have not completed a KIND Challenge activity, an additional multiple-choice question will be included to assess for what reasons the activity could not be completed (e.g., lack of time, that they forgot, illness, work, stress etc). Participants were then asked to reflect on the KIND Challenge overall including how meaningful and safe they found the challenge, how positive they felt after the challenge, and how connected and comfortable they felt towards their neighbours because of the challenge. These questions were specifically developed for the study (see Supplementary Table 1 - section c).

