### Adjusting for potential covariates

Several variables may need to be adjusted for in analyses examining the impact of the KIND Challenge and related objectives. This includes factors known to influence our primary outcomes such as: baseline community engagement, current Nextdoor platform activity, neighbour interactions since COVID-19, other COVID-19 social restrictions including level of social restrictions, and changes to face-to face interactions. Further adjustments may be needed to account for factors that may influence participation in the Challenge. These variables include measures of previous neighbour contact, and previous acts of kindness and the uptake of activities has to be accounted for, and pre-Challenge activities are measured. Post-Kind Challenge activity from number of activities take up, frequency, duration and impact of these activities are measured. An overall impact is also assessed and to understand if benefits of the KIND Challenge are sustained, we ask participants the same questions in relation to neighbour contact and the KIND Challenge activity uptake, frequency, duration, and impact.

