### Secondary outcomes analysis

The above ITT analysis using linear multiple regression modelling in Mplus 8.3, will be repeated for the secondary outcome of social isolation (H2) and the neighbourhood relationship quality outcomes H3 (a) social cohesion and trust (measured using the Social Capital Scale) at post 4-week intervention. For outcomes (b) perception that their neighbourhood is improving (categorised at improving, stable or declining), and (d) supportive, aversive, or ambivalent neighbour network classification, because those are categorical data, we will use a multi-nominal regression. Outcomes (c) higher importance around getting to know their neighbours (high and low importance), (e) neighbourhood conflict (no neighbourhood conflict and instances of neighbourhood conflict), and (f) number of neighbourhood contacts (0–5 and 6+ neighbourhood contacts) are dichotomous categorical data so we will use a binominal regression to explore ITT effects. Similarly, for all mental health secondary outcomes at post 4-week intervention, H4 (a) depression (b) social anxiety, (c) stress, (d) quality of life, and (e) positive affect, measured using the PHQ-8, Mini-SPIN, PSS-4, EUROHIS-QOL-8, and PANAS-PA respectively. The same model building approach will be adopted as in H1.

To model whether effects are maintained for all outcomes (H5) in the participants assigned to the KIND Challenge group, a series of within-group ANCOVAs will be run. Differences in baseline (T1), post-intervention (T2), and one-month follow-up (T3) outcomes will be analysed for both primary and secondary outcomes. A model building approach will be taken controlling co-variates outlined above for H1–4. The sustainability of the intervention (H6) will be explored to determine if the participants assigned to the KIND Challenge group continue with acts of kindness. Both the frequency and duration of KIND acts completed in the one-month follow-up, and the level of engagement for each type of activity completed (i) emotional support, (ii) tangible support, (iii) informational support, (iv) belonging support, and (v) companionship support will be analysed. A series of within-group ANCOVAs will be run using the frequency and duration of KIND acts completed post 4-week intervention and one-month follow-up, to determine if engagement is sustained.

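### H6 compares kind acts at post-intervention and one-month follow-up, but the two surveys ask about different sets of acts, so the comparison can mislead in either direction

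*Protocol article*

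**What the plan says.** - **Hypothesis.** In the protocol article, Objectives, H6 predicts that "participants assigned to the KIND Challenge will continue engaging in acts of kindness at one-month follow-up". This is about kindness in general, not about repeating a particular act.
- **Analysis.** Under Secondary outcomes analysis, H6 is tested in the Challenge arm by within-group ANCOVAs "using the frequency and duration of KIND acts completed post 4-week intervention and one-month follow-up, to determine if engagement is sustained". The same section also lists "Both the frequency and duration of KIND acts completed in the one-month follow-up, and the level of engagement for each type of activity completed", naming five types of support.
- **Post-intervention item.** Under Post-KIND challenge activity, "participants will be asked if they completed either their nominated KIND Challenge activity or any KIND Challenge activity over the past month". On multiple activities: "They can select more than one activity and will rate each activity according to those scales".
- **Follow-up item.** Under Follow up KIND challenge activity, "Participants are asked if they have *continued* with the Kindness activity, if so, which activity or activities they chose to continue". The emphasis on the verb is the document's own. Those who continued then report "how frequently they completed the activity (1 = once to 4 = more than 5 times"), plus duration. Those who did not continue give their reasons in a textbox; no frequency or duration is described for them.
- **Comparability.** Under Adjusting for potential covariates, the article says that, to see whether benefits last, "we ask participants the same questions in relation to neighbour contact and the KIND Challenge activity uptake, frequency, duration, and impact".

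**The concern.** A change score is interpretable only if both measurements ask about the same thing. Here the first survey counts any Challenge activity, and the second, as described, counts only activities carried on from before. Two groups who satisfy H6 as worded could be missed at follow-up: people who moved to a different type of support, and people who did nothing during the Challenge but started later.

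The results by support type are most exposed. If someone replaces tangible help with companionship, the fall in the first type is recorded, but the matching rise in the second may not be.

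The scoring adds a second problem. The lowest frequency code is one occurrence, so people who stop have no score. Whether the analysis leaves them out or sets them to zero changes the answer.

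At stake is the sustainability conclusion. H6 is a within-arm question, so the randomised comparisons in H1 to H4 and the primary outcome are not affected. But the first problem arises when the data are captured, and no analysis plan can recover acts that the survey did not ask about.

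**Working it through.** The plan states no figure on this point, so there is none to reproduce. The check sets the items side by side and then shows, under stated assumptions, how each problem acts.

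**Step 1. The items compared**

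| | Post-intervention | One-month follow-up |
|---|---|---|
| Who is asked about acts | Anyone who did the nominated or any Challenge activity in the past month | Anyone who continued |
| Which acts | All selected, each rated | Those the participant chose to continue |
| Frequency codes | 1 to 4 | 1 to 4 |
| Duration codes | 1 to 5 | 1 to 5 |
| Score if none | None described | None described |

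The scales match. The gate does not.

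**Step 2. Effect of the narrower gate**

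Assumptions, none of them from the documents:
- each of five types is done with probability 0.4;
- frequency codes 1 to 4 are equally likely (mean 2.5);
- true total engagement is identical at both surveys;
- a share *s* of acts moves to a type not done before, and the follow-up item does not record those acts.

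True mean total frequency score at both surveys = 5 × 0.4 × 2.5 = 5.0. Recorded at follow-up = 5.0 × (1 − *s*).

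| *s* | True follow-up | Recorded follow-up | Recorded / true |
|---|---|---|---|
| 0 | 5.0 | 5.0 | 1.00 |
| 0.1 | 5.0 | 4.5 | 0.90 |
| 0.2 | 5.0 | 4.0 | 0.80 |
| 0.3 | 5.0 | 3.5 | 0.70 |
| 0.5 | 5.0 | 2.5 | 0.50 |

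A simulation of 200,000 people gave the same ratios. The ratio is simply 1 − *s*, so it restates the assumed switching rate and is not evidence of its size. With a matched any-act item the ratio is 1.00 for every *s*.

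**Step 3. Effect of having no score for non-continuers**

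Assumptions: one activity; codes 1 to 4 equally likely at post-intervention (mean 2.50); continuers keep the same code; the probability of continuing is (1 − stop rate) + 0.12 × (code − 2.5), so low-frequency participants stop more often.

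*Stop rate 20%.* Probabilities of continuing for codes 1 to 4 are 0.62, 0.74, 0.86 and 0.98.
- True mean, stoppers as 0: (1 × 0.62 + 2 × 0.74 + 3 × 0.86 + 4 × 0.98) / 4 = 8.60 / 4 = 2.15.
- Mean among continuers: 2.15 / 0.80 = 2.69.

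*Stop rate 40%.* Probabilities are 0.42, 0.54, 0.66 and 0.78.
- True mean: 6.60 / 4 = 1.65.
- Mean among continuers: 1.65 / 0.60 = 2.75.

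True engagement falls from 2.50 to 2.15 or 1.65. The mean among those with a follow-up score rises to 2.69 or 2.75, and the paired change among continuers is zero.

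**Step 4. How the two problems interact**

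Setting non-continuers to zero cures Step 3 only if answering no to the continuation question means that no acts were done. Under the literal reading it does not: a switcher or late starter would also receive a zero. So the gate and the zero code need to be fixed together.

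**The case against.** **A reader might infer that engagement falls by construction, even if it is fully sustained.** The documents do not support this. Someone who carries on the same acts gets the same codes on the same scales, and the ratio in Step 2 is 1.00 when nothing is switched. A false fall needs switching or late starting, and a restrictive reading of the item. Nor is the test necessarily biased towards finding that engagement was not sustained; Step 3 shows the opposite error.

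**The wording may be broader than it looks.** The article paraphrases items set out in Supplementary Table 1, which is not shown. Continuing with the Kindness activity could mean kindness in general, and several activities can be named. The support types are broad, so a change of specific act need not change the type recorded. This stands as a limit on size: on the general reading, little or nothing is lost. It does not remove the difference between the two stems as the article describes them.

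**The follow-up item suits a hypothesis about continuing.** True for a simple proportion who continued. It does not justify comparing frequency and duration with an any-act score, overall and by type.

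**The same-questions statement may refer to the pre-Challenge items.** That reading is possible. But the pre-Challenge item, as described, asks whether an act of kindness had been completed, which is also an any-act question. The follow-up item differs from both.

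**The neighbour-contact question.** A reader may notice that it is described at follow-up but not at post-intervention. H6 does not use it, so nothing needs to change there.

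**Conclusion.** The mismatch is in the stated text: the post-intervention item is gated on any Challenge activity and the follow-up item on continued activity, yet H6 compares their frequency and duration directly. The difference therefore mixes a change of question with a change in behaviour.

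Neither size nor direction is established. Under the literal reading, the false fall equals the share of acts switched to new types: 0 to 50% if 0 to 50% is assumed. Late starters would add to it. If only continuers are analysed, the error runs the other way: in the illustration, no paired change while true engagement falls by 0.35 (2.50 − 2.15) or 0.85 (2.50 − 1.65) code points. Confidence is high on the mismatch and moderate at most on its consequence, because the exact item wording is not shown.

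The point is worth correcting because the remedy is cheap and the sustainability result could otherwise be misread.

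**What to change.** **If the follow-up survey can still be changed:**
- Ask the post-intervention question at one-month follow-up: any kindness activity over the past month, with the same type list and the same frequency and duration scales.
- Score no activity as 0 at both surveys, overall and for each type.
- Keep whether each act was a continuation as a follow-on question.
- Run H6 on the any-act item.

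The cost is one reworded question stem, one follow-on question and a scoring rule. Repeating the post-intervention question without the zero would leave the second problem in place.

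**If data are already collected**, which is likely since Trial status gives an end date of 31 January 2021:
- Limit H6 to the proportion who continued Challenge activities.
- State that newly started acts may not have been captured.
- Reconcile the same-questions statement under Adjusting for potential covariates with the descriptions under Post-KIND challenge activity and Follow up KIND challenge activity.

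This costs a few sentences and a narrower claim.

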### Adjusting for potential covariates

Several variables may need to be adjusted for in analyses examining the impact of the KIND Challenge and related objectives. This includes factors known to influence our primary outcomes such as: baseline community engagement, current Nextdoor platform activity, neighbour interactions since COVID-19, other COVID-19 social restrictions including level of social restrictions, and changes to face-to face interactions. Further adjustments may be needed to account for factors that may influence participation in the Challenge. These variables include measures of previous neighbour contact, and previous acts of kindness and the uptake of activities has to be accounted for, and pre-Challenge activities are measured. Post-Kind Challenge activity from number of activities take up, frequency, duration and impact of these activities are measured. An overall impact is also assessed and to understand if benefits of the KIND Challenge are sustained, we ask participants the same questions in relation to neighbour contact and the KIND Challenge activity uptake, frequency, duration, and impact.

#### Community engagement [49]

Questions were designed to assess an individual’s involvement in cultural and community-based groups/activities in the past year. The measure consists of two subscales with 2 and 7 items respectively and assesses the frequency with which an individual attends cultural and community events, groups, or activities. The measure employs a 3-point ordinal scale ranging from 0 (less than once a year) to 2 (every few months or more). Both “community cultural engagement” and “community group engagement” subscales have been shown by Fancourt et al. [49] to have good reliability and internal consistency (cultural engagement Cronbach’s alpha = 0.74, group engagement alpha = 0.69).

#### Nextdoor platform activity

A list of questions were developed to determine how participants currently engage with the Nextdoor platform. The measure consists of up to 9 items which include which will ask how long a user has been a member of Nextdoor ranging from 1 (less than 1 week) to 6 (more than 5 years), how many active and passive hours the participant has spent on the platform in the past month on a scale of 1 (less than 1 h) to 4 (more than 9 h). The last item relates to a change in Nextdoor platform activity due to the COVID-19 pandemic using a dichotomous yes/no response. If yes, participants will be asked if they have spent more or less time on the Nextdoor platform. These questions were specifically developed for the study (see Supplementary Table 1 – section g).

#### Neighbour interactions since COVID-19

Questions were developed to evaluate how the COVID-19 pandemic has influenced interactions between neighbours. The participants will be asked about their current contact with their neighbours, specifically if overall frequency of contact has changed from 1 (no change), 2 (in contact with neighbours more) or 3, (in contact with neighbours less). If participants select that they have been in contact with their neighbours more, they are asked about the contact modality (e.g., in person, at a safe distance, via phone text, videocall or other communication device etc.). We will also assess participant’s worries about their health, other people’s health, interaction avoidance, additional methods of communication to get in touch, meaningfulness of the relationship rated on a 1 (no worries/ not done/ strongly disagree) to 10 (worry a lot/ done this a lot/ strongly agree) Likert scale. These questions were specifically developed for the study (see Supplementary Table 1 – section h).

#### COVID-19 social restrictions

This measure was designed to assess the impact of the COVID-19 pandemic on immediate social interactions. Social restriction severity will be measured by the number of different government restrictions relevant to the participant at time of survey (from a list of 13 types of restrictions). This list consists of a variety of imposed restrictions including social, travel, retail, and education. These questions were specifically developed for the study (see Supplementary Table 1 – section i).

#### Pre-KIND challenge neighbourhood contact and previous kindness activity

Prior neighbourhood contact may influence both the primary outcome and participation in the Challenge. Thus, participants will be asked if they have been in contact with their neighbour safely in person or using a digital communication device (Yes/No). They are then asked if they had completed an act of kindness before being assigned to the Challenge. If yes, participants will be asked how frequently they completed the activity (1 = once to 4 = more than 5 times), the duration of the activity (1 = less than 10 min to 5 = more than 2 h) and how connected they feel to their neighbours because of the activity (1 = not at all connected to 10 = very connected). These questions were specifically developed for the study (see Supplementary Table 1 – section j).

